#### Medication adherence

Analyses will assess both for a one-time effect of the intervention on adherence and for a change in the rate of change in adherence over time. Appropriate statistical adjustments will be made to account for multiple observations (at each three-month interval) on the same individuals. Our basic model will be a segmented multiple time series regression, as specified in figure 2.

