**Methods:**

The FOD trial includes 2,507 employees and dependents with diabetes insured by one large employer. Approximately 81% are enrolled in a single independent-practice association model health maintenance organization. The control group includes 8,637 patients with diabetes covered by other employers and enrolled in the same managed care organization. Both groups received written materials about the importance of adherence to secondary prevention therapies, while only the intervention group received targeted co-payment reductions for glycemic agents, antihypertensives, lipid-lowering agents, antidepressants, and diabetic eye exams. Primary outcomes include medication uptake and adherence. Secondary outcomes include health care utilization and expenditures. An interrupted time series, control group design will allow rigorous assessment of the intervention's impact, while controlling for unrelated temporal trends. Individual patient-level baseline data are presented.

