### Study design

The study employs an interrupted time series design, with medication adherence rates assessed at three-month intervals (unit of observation is the patient-quarter), beginning 30 months prior to the intervention (the 'pre' period) and continuing through the duration of the 30-month intervention (the 'post' period). This study design provides a strong test of the intervention's impact on medication adherence, separate from other ongoing temporal changes in adherence [34]. The advantage of this 'difference-in-difference' design is that any change in the control group values may reflect naturally occurring changes over time (perhaps due to policy or medical care changes), while any change in the UM intervention group values will reflect both the same naturally occurring trends, as well as the impact of the value-based co-payment reductions.

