#### Health care expenditures

To implement the 'difference in difference' approach to examining health care costs, we will use the same multiple time-series regression approach specified above. Initial cost models will use ordinary least squares with a log transformation of costs to account for the skewness of the distribution of health care expenditures. We will test two-part econometric models against the one-part model because the unit of analysis is the patient quarter, and there may be several individuals with no spending in any given quarter. The first part model will be a logit/probit modeling the probability of non-zero expenditure, and the second part will model expenditure conditional on non-zero spending [41].

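### The stated variance adjustment covers only repeated measures within a patient, so irregular quarterly movement specific to one group can be declared a co-payment effect too often

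*Protocol article*

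**What the plan says.** Under Study design, the article sets the unit of analysis: "medication adherence rates assessed at three-month intervals (unit of observation is the patient-quarter"). The same section gives the span of the series: "beginning 30 months prior to the intervention (the 'pre' period) and continuing through the duration of the 30-month intervention (the 'post' period"). That gives 10 quarters before and 10 after the start. Under Statistical analyses, Medication adherence, the model tests for a "one-time effect of the intervention on adherence and for a change in the rate of change in adherence over time", and the only dependence mentioned is within the patient: "Appropriate statistical adjustments will be made to account for multiple observations (at each three-month interval) on the same individuals". For costs, under Health care expenditures, "we will use the same multiple time-series regression approach specified above".

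The Abstract gives the group structure: "The FOD trial includes 2,507 employees and dependents with diabetes insured by one large employer" and "The control group includes 8,637 patients with diabetes covered by other employers and enrolled in the same managed care organization". Study setting adds that the two groups have different pharmacy benefits managers, both working on the same claims platform.

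The case for attributing a difference to the co-payments rests on the control series. Study design says that "any change in the UM intervention group values will reflect both the same naturally occurring trends, as well as the impact", meaning here what the lower co-payments achieve. The third limitation in the Discussion adds that this protection fails if a market factor reaches only one group when the intervention starts.

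**The concern.** A patient-level correction treats each group's mean in a quarter as its fitted line plus sampling noise from independent patients. With over a thousand users of a drug class in the smaller group, that noise is small. Any irregular movement specific to one group (a quarter in which UM refills run high, say, or a run of such quarters) does not average out over patients, and enrolling more of them does not shrink it. It enters the estimated level and slope changes but not their standard errors.

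This differs from the bias that the Discussion concedes. That bias needs an outside event to coincide with July 2006. The understated standard error arises from ordinary fluctuation in any of the 20 quarters. At stake is whether a significant level or slope change in adherence, a primary outcome, can be told apart from group-level noise.

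**Working it through.** **1. The plan's own power figures.** The article gives 2,131 and 4,000 patients, 80% power and p = 0.05. With independent patients and a two-sided test, the detectable change is 2.80 × √[p(1−p)(1/2131 + 1/4000)].
- Uptake, p = 0.50: 2.80 × 0.01341 = 3.8 points (stated: 3.8).
- MPR, p = 0.65: 2.80 × 0.01279 = 3.6 points with a common variance, or 3.54 with separate variances (stated: 3.5).

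Both reproduce with no shared group error. Adding a treated-minus-control shock with a standard deviation of 1 point inside the root moves them from 3.8 to 4.7 and from 3.6 to 4.5 points.

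**2. Inputs for the segmented model.**
- From the documents: 10 + 10 quarters. ACE/ARB users from Table 2: 43.4% of 2,507 = 1,088 and 48.7% of 8,637 = 4,206. Statin users (about 1,121 and 3,843) give nearly the same results.
- Assumed: MPR standard deviation 30 points, or 47.7 (= √(0.65 × 0.35), the value that goes with the plan's MPR power figure); within-person correlation 0.5; drift in the UM-minus-control difference with standard deviation τ and lag-1 correlation ρ; no true effect.

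**3. Patient-level standard error.** The variance of one quarterly difference that matters for change is v = SD² × (1 − 0.5) × (1/1088 + 1/4206). For SD 30, v = 0.521. In a 20-point regression with intercept, trend, level change and slope change, the level-change variance is 0.812v, so the standard error is √(0.812 × 0.521) = 0.65 points. For SD 47.7, v = 1.316 and the standard error is 1.03 points.

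**4. Adding group-specific drift.** Drift adds 0.812τ² to the level-change variance at ρ = 0 and 1.291τ² at ρ = 0.5. True rejection of the nominal 5% test is 2[1 − Φ(1.96 × SE_patient / SE_total)].

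Example: SD 30, τ = 1, ρ = 0.5. SE_total = √(0.423 + 1.291) = 1.31. The ratio is 0.65/1.31 = 0.497, and 2[1 − Φ(0.973)] = 33%.

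Level-change test, true rejection rate (%):

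| τ (points) | SD 30, ρ = 0 | SD 30, ρ = 0.5 | SD 47.7, ρ = 0 | SD 47.7, ρ = 0.5 |
|---|---|---|---|---|
| 0.25 | 6.4 | 7.2 | 5.5 | 5.9 |
| 0.5 | 10.7 | 14.0 | 7.2 | 8.6 |
| 1 | 25.1 | 33.0 | 14.0 | 18.7 |
| 2 | 50.6 | 59.0 | 32.9 | 41.7 |

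The slope-change test has the same rates at ρ = 0. At ρ = 0.5 it is worse: 8, 17, 39 and 64% for SD 30.

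**5. Simulation check.** Patient-level data analysed with patient-clustered standard errors (600 runs, SD 30) rejected 5.2% with no drift and 31% at τ = 1, ρ = 0.5, in line with the algebra.

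**6. Does the remedy work?** Analysing only the difference series does not restore 5%: such fits rejected about 8 to 12%, because 20 points estimate autocorrelation poorly. Requiring significance in both the patient-clustered and the AR(1) difference-series tests, which is what reporting the wider interval amounts to, gave about 3 to 10%, against 5 to 59% for patient clustering alone.

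**The case against.** The strongest reply is that the sentence promises one adjustment and does not exclude others. The model equation is in Figure 2, which was not available to this review, and a fuller analysis plan may add quarter terms or autocorrelated errors. This stands as a limit: a reader might infer that the plan has ruled out any other correction, and the text does not say so. But the article does name the dependence it will correct, that dependence is too narrow for a single treated employer, and the power figures rest on the same independence.

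A reader might also infer that all drift among UM members will be read as a co-payment effect. The documents do not support that. Movement common to both groups is removed by the control series, and about 81% of active UM members are in the same HMO as the controls, so local prescribing changes or drug news would largely reach both. Both benefits managers use one claims platform, which weakens claims timing as a source. Steady linear drift is absorbed if group trends are modelled, as the level-and-slope analysis implies.

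The size is assumed, and this objection also stands. It would be wrong to say that the error rate at least doubles at 0.5 point: with SD 47.7 the level test rejects only 7 to 9% there. At 0.25 point the problem is minor. Nothing was computed for log costs, so the point carries over to the cost models in kind only.

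**Conclusion.** The point holds in a conditional form. The one adjustment named leaves irregular or autocorrelated group-specific movement with no variance, and neither the control series nor the Discussion's caveat supplies it. If such movement exists, intervals for the level and slope changes are too narrow. For the level test, under the stated assumptions, true rejection of a nominal 5% test is about 6 to 7% at a drift standard deviation of 0.25 point, 7 to 14% at 0.5, 14 to 33% at 1 and 33 to 59% at 2. A drift of 1 point is well below the 3.5-point effect that the trial is sized to detect, so the upper rows cannot be dismissed, but no passage shows that drift of that size occurs. The change is worth making before the outcome analysis, which the article says awaits the end of the 30-month window.

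**What to change.** Keep the patient-clustered analysis. Alongside it, form the covariate-adjusted UM-minus-control mean for each of the 20 quarters and fit the same segmented model to that series with autocorrelated errors (for example AR(1) by REML) and t critical values on about 16 degrees of freedom (20 quarters minus 4 coefficients). Report the wider of the two intervals for the level and slope changes. The series fit should not replace patient clustering, because alone it rejects too often. If employer codes are available, apply the same model to each large control employer as a placebo and show where the UM estimate falls among them. Say that the same two-level inference applies to the cost models.

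The cost is a few sentences of analysis wording and a few hours of programming on data already being collected. The downsides are wider intervals, some remaining inflation (up to about 10%) when drift is strongly autocorrelated, and slight conservatism when there is none. For a 3.5-point level change with SD 30, simulated power of the difference-series test was 99% with no drift, 96% at drift 0.5 and 78% at drift 1 (ρ = 0.5); power under the wider-interval rule cannot exceed these values.

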**Figure 2 F2:**
[figure not shown]
**Segmented multiple time series regression model**.

#### Health care expenditures

To implement the 'difference in difference' approach to examining health care costs, we will use the same multiple time-series regression approach specified above. Initial cost models will use ordinary least squares with a log transformation of costs to account for the skewness of the distribution of health care expenditures. We will test two-part econometric models against the one-part model because the unit of analysis is the patient quarter, and there may be several individuals with no spending in any given quarter. The first part model will be a logit/probit modeling the probability of non-zero expenditure, and the second part will model expenditure conditional on non-zero spending [41].

#### Subgroup analyses

Because depression is associated with worse adherence and higher costs in individuals with diabetes [12-15], subgroup analyses will be performed to explore for a differential effect of the intervention in those with depression. In turn, because there may be important differences between UM employees who enroll in M-CARE and those who enroll in other health plans, analyses will be repeated with and without the small subset enrolled in other health plans.

## Results

### Sample characteristics

Over the first year, a total of 2,507 UM employees and dependents with diabetes were included in the intervention program, while 8,637 employees with diabetes and dependents with diabetes of other employers were identified for the control group. Table 2 shows the baseline characteristics of both groups. The mean age was 45.1 years in the intervention group and 47.5 years in the control group. The intervention group had slightly more women than the control group (57.7% versus 53.1%), but health was comparable between the two groups, with Charlson scores of 1.43 and 1.46 in the intervention and control groups, respectively. The baseline rates of metformin and statin use were similar between the two groups. In contrast, baseline SSRI use was significantly higher (21.7% versus 18.9%), and ACE/ARB use significantly lower (48.7% versus 43.4%, P < 0.01) in the intervention group relative to the controls.

**Table 2 T2:** Baseline characteristics of the MHealthy: focus on diabetes sample

**Characteristics**	**Reduced Co-payments (Intervention)**	**Standard Co-payments (Control)**
**Number of respondents enrolled**	2,507	8,637

**Mean age in years (SD)**	45.1 (13.06)	47.5 (12.83)*

**Female**	57.7%	53.1%*

**Basis for insurance coverage**		
**Employee**	62.3%	66.3%*
**Spouse**	31.1%	29.1%
**Child**	4.7%	4.0%
**Other**	1.9%	0.6%

**Median Household Income**^†^	$55,086	$54,758

**Charlson Comorbidity Score**^‡^**(SD)**	1.43 (0.65)	1.46 (0.69)

**Baseline Medication Utilization**		
**Metformin**	53.9%	53.6%
**ACE/ARBs**	43.4%	48.7%*
**Statins**	44.7%	44.5%
**SSRIs**	21.7%	18.9%*

*Significant at P < 0.05

^†^Based-upon zip-code level median household income data

^‡^Estimates based on the Deyo modification to the Charlson Index [40].

### Acceptability of intervention

The FOD Trial was successfully implemented on 1 July 2006. Comprehensive data is currently being collected and will be fully analyzed upon completion of the 30-month intervention window. The automatic enrollment design was well-received, with very few individuals choosing to opt-out of the program. Numerous e-mail testimonials have been received from employees and dependents that have benefited from the program. In addition, the intervention has been very well-received by various stakeholders including those at the University of Michigan [35,42] and the Michigan state legislature [43], who have expressed interest in expanding such programs to other chronic diseases, pending the results of this trial.

## Discussion

As health care costs continue to rise, payers are increasingly shifting costs to patients through higher deductibles and co-payments [32]. Yet, uniform increases in co-payments may curb the use of both low-value and high-value therapies alike, potentially resulting in adverse health consequences in individuals with chronic diseases [18,44]. VBID has been proposed specifically to offset the adverse clinical effects of rising out-of-pocket costs, by setting the patient co-payment amount relative to the value – not exclusively the cost – of the therapy [28-31]. While several large employers and insurers are experimenting with VBID type programs, there have been no prospective controlled evaluations of the impact of such programs in actual practice.

This trial is the first of its kind – an intervention of targeted co-payment reductions for specific high-value therapies in specific high-risk patients – designed both to improve adherence to evidence-based therapies by patients with diabetes in the workforce, but also to allow for rigorous evaluation of the program's effectiveness. The trial's progress to date has demonstrated the feasibility of implementing targeted, value-based benefit design changes in practice. The automatic opt-in design of the intervention has created near unanimous participation. No significant barriers to implementation have been encountered to date, and the intervention continues to receive strong employee-level and institutional-level support at UM. Planned analyses will determine the intervention's impact on the uptake of and adherence to evidence-based medications, as well as the impact on the use and cost of both pharmaceutical and non-pharmaceutical health services.

This study has some limitations. First, determining the effect of the co-payment reductions above any effects due to secular trends in adherence can be difficult. Second, although the control group was identified from the same health plan using the same selection criteria used to identify the intervention group, differences remain between these two groups because randomization was not part of the study design. That noted, the interrupted time series, control group design was specifically chosen because it provides a strong test of whether the copayment reductions impact on medication adherence, separate from other ongoing temporal changes in adherence or baseline differences between the two groups [34].

Third, this trial is taking place in an evolving health care marketplace, which may make it more difficult to isolate the effect of the intervention from other ongoing benefit design changes or quality-improvement initiatives. Again, FOD's interrupted time series control group design offsets this concern, to the extent possible, and is a key methodological strength of the trial. By assessing outcomes for an intervention and a control group at multiple times both before and after the intervention, we capture and can control for temporal trends due to other market factors, provided they do not occur in only one of the two groups at the same time as the intervention is implemented.

Fourth, adherence is estimated using medication possession ratios, which assume that the supply of medication dispensed is an adequate proxy for patient adherence. However, because the intervention should have a direct effect on pill-buying but only an indirect effect on pill-taking, MPR is likely to modestly overestimate actual adherence, by causing some unknown number of patients to buy but not take their medications. Further, if physicians instruct patients to take medications differently than prescribed, or if medications are stockpiled or conversely lost, MPR may be an imperfect measure. However, the use of MPR as a measure of adherence for controlled trials has been validated by Steiner and colleagues and is used extensively in clinical research [45]. Fifth, the trial focuses on individuals with diabetes with employer-based health insurance. While over 62% of the non-elderly U.S. population has employer-based coverage [46], there is tremendous heterogeneity in employer benefit packages and in the health risk profiles of employees, potentially limiting generalizability.

Sixth, a common difficulty with any policy intervention is assessing for unintended consequences (or externalities) which may arise as a result of the intervention. To the extent we have anticipated them, we will examine for potential externalities, such as formulary tier-shifting, in which individuals shift from lower to higher tier drugs in response to the co-payment reductions. Our intervention maintained a cost advantage for using lower tiers, but the extent of tier-shifting remains an empirical issue that we will explore.

Finally, a practical issue related to the likely uptake of VBID-type interventions merits mention. With health care costs rising rapidly, payers are looking for ways to constrain cost growth, potentially limiting the appeal of benefit design alterations which shift pharmaceutical costs back to the employer from the patient. For the most part, employers want to see a positive return on investment, which is unlikely when framed solely in financial terms. However, the true return on investment in health care is health. When framed in these terms, employers should expect and even demand a positive return on investment.

In conclusion, we have described the rationale, design, and implementation of a prospective controlled trial designed to test the effectiveness of targeted, value-based co-payment reductions in improving medication adherence among a population of individuals with diabetes covered by employer-sponsored health insurance. Findings from this study should provide needed insight into the responsiveness of patients' medication-taking behaviors to targeted reductions in out-of-pocket costs, as well as the impact on both pharmaceutical and overall health care utilization and spending. This study is quite timely given rapidly rising health care costs, increasing use of consumer-directed health care (with its high cost-sharing requirements), and continuing pervasive quality gaps between the optimal use of high-value chronic disease therapies and their actual use in practice [47,48]. Data from this study will provide payers with needed insights into the role of VBID to mitigate the adverse health consequences of underuse due to high out-of-pocket expenditures, while continuing to use cost-sharing to discourage overuse.
